## Abstract

Systematic reviews have demonstrated the scarcity of well-designed evaluations investigating outdoor nature-based play and learning provision for children in the early learning and childcare (ELC) sector among global Western countries. This study will examine the feasibility and acceptability of the programme and the evaluation design of outdoor nature-based play and learning provision across urban ELC settings in a Scottish metropolitan city. Six ELC settings with different outdoor nature-based play delivery models will be recruited. One trial design will be tested: a quasi-experimental comparison of children attending three different models of outdoor play and learning provision. Measures will be assessed at baseline and five weeks later. Key feasibility questions include: recruitment and retention of ELC settings and children; suitability of statistical matching based on propensity score; completeness of outcome measures. Process evaluation will assess the acceptability of trial design methods and provision of outdoor nature-based play among ELC educators. These questions will be assessed against pre-defined progression criteria. This feasibility study will inform a powered effectiveness evaluation and support policy making and service delivery in the Scottish ELC sector.

## 1. Introduction

The early learning and childcare (ELC) environment is an important setting to support healthy child development. Providing outdoor nature-based play and learning in the early years (0 to 5 years) setting can encourage children to be physically active and develop their social and cognitive skills, while helping them maintain a healthy weight later in life and support more equitable access to local green spaces [1]. However, there is a growing concern that the increasing availability of tablets, smart phones, and television watching, along with a high number of risk averse parents, is culminating in children who are less physically active, who are spending a lot of time indoors, and who have interrupted sleep patterns [2,3,4]. By providing children with more time outdoors in rich green spaces, nature-based ELC could be a key approach for supporting children’s physical, social, and emotional development.

The UK Chief Medical Officers recommend that preschool-aged children (3–4 years) should spend at least 3 h per day physically active, including 1 h in moderate-to-vigorous physical activity (MVPA) [5]. However, research suggests that preschool-aged children struggle to meet the recommendations for MVPA and spend most of their time in low physical activity (PA) [6,7]. MVPA is associated with positive mental health, cardiorespiratory fitness, and body mass index (BMI) in adolescence, therefore it is important to promote these healthy behaviours in the early years [8,9]. Being outdoors is a positive correlate for PA in children [10]. Furthermore, PA, especially outdoor play, is positively associated with most sleep outcomes in preschool-aged children [11]. The natural outdoor environment has a variety of affordances that have the potential to support children’s development of their motor competence, social skills, mental wellbeing, and physical health [10,12,13,14]. A recent review of the literature found positive associations for sedentary time and balance (a key component of motor competence) among children attending nature-based ELC [15]. However, the authors concluded that more high-quality research is required that better describes the nature exposure and outcome measurement tools [15].

Providing children with opportunities to spend time outdoors engaging in unstructured play, especially in nature, is a potentially effective approach for supporting emotional and social resilience and cognitive and physical development [16,17,18]. Through play outdoors, children can engage in a variety of play behaviours that help them learn how to navigate their socio–cultural environments in safe simulations [19]. Furthermore, research suggests that long exposure to natural outdoor environmental lighting (i.e., sunlight) may have a beneficial impact on children’s behavioural and cognitive development [20,21]. The affordances of the natural outdoor environment such as open fields, trees, vegetation, and hilly terrain encourage children to be physically active, imaginative, expressive, and to explore their surroundings, having a beneficial impact on their social skills, mental wellbeing, and cognitive outcomes [1,13,19,22,23]. 

Risk-taking during play exposes children to excitement, uncertainty, and sometimes the possibility of injury [24,25]. Through observations and interviews, researchers have identified eight categories of risky play: play with great heights; play with high speed; play with dangerous tools; play near dangerous elements; rough-and-tumble play; play where children go exploring alone; play with impact; and vicarious play [24,25,26]. By challenging themselves during play, children can manage uncertainties while avoiding excessive risk taking, helping them to develop the skills required to support their increasing autonomy and independence [27]. Nonetheless, although risky play is supported within the Scottish Government’s resources (*My World Outdoors* [28]), support of this type of play behaviour, and others, varies based on practitioners’ beliefs and understanding of outdoor nature-based play and learning provision [29]. The authors are not aware of any attempt in the literature to explore play behaviours and risk-taking opportunities among children attending urban ELC settings in Scotland. 

The role of the practitioner is crucial for supporting quality outdoor play and learning experiences for children, since their beliefs and attitudes influence their practice and values [3,29]. This has implications for how children utilise their outdoor space and the type of outdoor space children have access to (e.g., forest, park, structured outdoor playground). Furthermore, training for practitioners in the provision of outdoor play and learning is not universal, and attitudes and beliefs towards how outdoor nature-based provision should be incorporated into everyday practice varies [30]. Therefore, it is important to understand how practitioners within these ELC settings perceive the ability to incorporate outdoor play and learning within their regular everyday practice.

Most of the research investigating the relationship between nature-based play provision and children’s health outcomes targets older children (greater than 7 years); there is less available evidence for children in the early years (0 to 7 years) within the preschool/kindergarten setting. Much of the available evidence for this population and context suffer from poor methodological quality due to poorly designed evaluations [10,17]. These evaluations are often uncontrolled interventions or cross-sectional studies, with small sample sizes, limited reporting of confounding variables, and poor reporting of the reasons for participant withdrawal, leading to results with a high risk of bias. Evaluations in this field require more sound methodology that can be more effectively achieved by firstly assessing the feasibility of potential evaluation designs.

Feasibility studies have been carried out in British ELC settings before; however, they have focused on interventions specifically targeting obesity prevention through PA and/or healthy eating [31,32,33]. As far as the authors are aware, there has not yet been any formal robust evaluation of outdoor nature-based play and learning provision in the British early years sector. However, such an evaluation has several unique uncertainties that firstly require examination within a feasibility study, including recruiting ELC settings that provide nature-based play and learning, recruitment of participants in these settings, participant randomisation processes, and outcome measures.

In Scotland, all 3- and 4-year-old children (and eligible 2-year-olds) are entitled to 1140 h of funded ELC per year [34]. This is part of the Scottish Government’s commitment to reduce the educational attainment gap and social inequalities in Scotland by providing families with equal access to early years childcare. In 2021, 97% of eligible children were registered for funded ELC [35]. Therefore, the centre-based childcare setting is an opportunity to support the development of lifelong healthy behaviours at the population level.

The ELC sector in Scotland provides several formal settings where play and learning take place. They provide different opportunities for exposure to the outdoors with a variety of activities children can engage in while outdoors. These include: (i).*Fully outdoor* setting, where children spend most of their time in a forest or park with many natural affordances;(ii).*Indoor/outdoor*, where children can move freely between the indoor and outdoor area of their ELC setting; (iii).(*Satellite*, where the ELC has a nature space (e.g., forest or park), but it is not on their physical premises; (iv).*Traditional* ELC setting, often attached to a primary school, where children spend most of their time indoors but with the opportunity to experience the outdoor environment (built and/or natural) as part of structured sessions or play breaks.

The objective of the current feasibility study is to trial a quasi-experimental non-equivocal control design using three models of outdoor play and learning provision in the Scottish early years sector: fully outdoors, satellite, and traditional ELC settings. The aim of this study is to determine whether prespecified criteria associated with the feasibility and acceptability of the program and trial design methods are met sufficiently to progress to a full powered effectiveness evaluation.

## 2. Materials and Methods

The reporting of this protocol has endeavoured to follow the Standard Protocol Items: Recommendations for Interventional Trials (SPIRIT) statement (see Supplementary Table S1) [36]. We took a systematic pre-evaluation approach to designing this feasibility study by carrying out two initial phases to identify the most appropriate research questions.

### 2.1. Initial Phases

#### 2.1.1. Phase One: Development of Logic Model

Using secondary data analysis and triangulation methodology, we developed a Theory of Change (ToC) of how nature-based ELC functions in a Scottish urban city, Glasgow. We triangulated interview and focus group transcripts of parents whose children attended nature-based ELC settings in the West of Scotland, observation schedules of children playing outdoors at nature-based ELC settings in the West of Scotland, and international studies investigating the relationship between nature-based ELC settings and children’s health and wellbeing outcomes from several high-income countries. This approach allowed us to explicitly state the inputs, activities, outputs, outcomes, and underlying assumptions associated with the delivery of the programme. Further details of this process can be found elsewhere (Traynor et al., 2022). This process identified key components regarding provision of nature-based ELC that required further investigation with stakeholders before an evaluation design could be developed.

#### 2.1.2. Phase Two: Evaluability Assessment with Key Stakeholders, Refinement of Logic Model, ToC, and Identification of Evaluation Goals

This phase followed a systematic approach to conducting an Evaluability Assessment (EA). The purpose of these EA workshops was to refine the ToC developed in Phase One, ensuring that it was still relevant to the current context (e.g., COVID-19 pandemic, rollout of 1140 h free childcare entitlement), and to identify the evaluation questions that key stakeholders would like answered regarding the provision of nature-based ELC in Scotland. These workshops took place online using MS Teams due to the government COVID-19 guidelines restricting in-person contact at the time.

During analysis of the workshop outputs, several uncertainties associated with the design of an impact evaluation were identified. These included recruitment methods of ELC settings and participants, retention rates of participants, possibility of randomisation, and type of outcome measures. These uncertainties were presented to the research steering group and a decision was made regarding how to address them. The steering group was composed of representatives from the local authority and a third sector organisation involved in the delivery of early learning and childcare in Scotland. The steering group guided the design of the research project, ensuring that the design was appropriate for the early years setting. It was decided that these uncertainties should be addressed in a feasibility study before investing finite resources into a powered effectiveness evaluation.

Six research questions were developed to be addressed in this feasibility study of nature-based ELC. Table 1 outlines these research questions along with how they will be addressed.

### 2.2. Study Design

#### Feasibility and Pilot Study

The development of this feasibility study is based on guidance from the UK Medical Research Council for developing and evaluating complex interventions [37]. This study will pilot a quasi-experimental study design method:

A quasi-experimental non-equivalent control design using propensity score matching with multiple treatment groups. Children who attend two traditional ELC settings will be assigned to the control group and matched with children from two treatment groups: (1) 2 fully outdoors ELC settings and (2) 2 satellite ELC settings. The researchers will follow guidance on implementing propensity score methods with multiple treatment groups (e.g., 2 exposure groups and a control group) [38]. From baseline to follow-up, the study duration will be 5 weeks. Play and learning will continue as normal in both settings and the outcomes mentioned below will be measured to assess the possible impact of outdoor play and learning.

This study will employ a mixed-methods approach. Both quantitative and qualitative data will be collected to address the research questions. Alongside the piloting of these two study designs, we will carry out a process evaluation using semi-structured interviews. Qualitative methods are considered an important methodological approach to understanding the causal mechanisms of complex health interventions [39].

### 2.3. Ethics Approval

Ethical approval has been provided by the College of Social Science, University of Glasgow (application number: 400210145) and Glasgow City Council (reference number: 21.26).

### 2.4. Setting

Glasgow is the largest metropolitan area in Scotland and one of the most socioeconomically disadvantaged areas in Western Europe, with more than a third of the cities’ children estimated to be living below the poverty line [40]. The Glasgow City Council (GCC) area has one of the highest numbers of nature-based ELC settings in Scotland, with at least 18 ELC settings registered or in the process of becoming registered by the Care Inspectorate as a provider of a specific nature-based ELC model [41].

The GCC area has 110 ELC settings that are operated by the GCC Education Services and over 300 ELC settings that are privately or voluntary operated. Within these settings, there are several that are registered with the Care Inspectorate as a satellite model or are in the process of becoming registered. There are around six functioning as fully outdoor nature-based models in the GCC area, with more across Scotland. Many of these are private and voluntary childcare providers, with some functioning in partnership with GCC. Partnership providers are social enterprises that work collaboratively with GCC to extent their ELC provision. The Scottish Government’s 1140 h of free childcare entitlement is applicable to all ELC providers with the caveat that some private and partnership settings request that parents cover some additional costs. Furthermore, each setting is based in a different area of Glasgow, uses different types of green/natural spaces, and varies in size with regards to the number of attending children and practitioners. All of these factors, in addition to context, dose, and practice will influence the daily operations of each ELC setting and thus will be investigated in this feasibility and pilot study.

In the GCC local authority ELC settings, there are between 20 and 100 three- to five-year-olds registered at any one time with an average of 60 or 38 children per setting, depending on whether the ELC setting operates 50 or 38 weeks per year, respectively. In the private, voluntary, and independent sector, ELC settings have between 12 and 80 three- to five-year-olds registered, with an average of around 30 children enrolled at any one time.

### 2.5. Participants

ELC settings in the GCC area, representing the different models previously mentioned, will be invited to participate in the study, including their headteacher/manager and 2 practitioners. Figure 1 illustrates the study flow diagram.

#### Inclusion and Exclusion Criteria

The inclusion and exclusion criteria (Table 2) are to ensure that children who are enrolled in the study are as similar as possible to children who would be enrolling in the ELC setting for the first time at the beginning of the academic year (the timepoint at which a full-scale evaluation would be recruiting). Eligible children are those who attend these ELC settings, are 3 years old, and have consent from their parent/carer to participate. Participants will receive a voucher of GBP £10 as a token of appreciation for their participation. Participating ELC settings will receive a GBP £100 donation and an additional GBP 10 for each ELC educator that participates in the interviews.

### 2.6. Sample Size

As this is a feasibility/pilot study, no sample size to detect between group differences was calculated. The study may provide preliminary data for the calculation of a sample size for a future full-scale evaluation. We aim to recruit 2 fully outdoor ELC settings, 2 satellite ELC settings, and 2 traditional ELC settings.

A minimum of 10 children per ELC setting will be recruited. Two practitioners and one headteacher/manager will be recruited from each ELC setting.

The propensity score is the probability of being exposed given the values of measured confounding variables [42]. In the same manner that randomisation will on average lead to measured and unmeasured covariates being balanced between study groups, assigning participants based on their propensity score will on average lead to measured baseline covariates being balanced between the study groups [43]. Our propensity score model will include all measured baseline covariates collected in the demographic survey. Participants from the traditional ELC settings (comparison) will be matched with participants from the fully outdoor settings and satellite settings (exposure) with similar propensity scores. We will use nearest neighbour matching within a specified caliper distance that is proportional to the standard deviation of the recorded covariates [43]. Once matched, the treatment effect will be determined by directly comparing the outcome data between matched samples of the exposure and comparison groups. Researchers have shown that the use of propensity score matching with small study samples can demonstrate unbiased estimations of treatment effect if the appropriate confounding variables are included in the propensity score model [44].

### 2.8. Measures

The feasibility questions that this study will address are shown in Table 1. **RQ1** intends to address the uncertainties associated with recruitment and retention of ELC settings and study participants. The following data will be collected across all participating ELC settings:Number of eligible ELC settings that were approached to participate in the study.Number of ELC settings that expressed an interest in taking part, number of ELC settings that declined an invitation to take part, and number of ELC settings that did not respond.Number of eligible children who were approached to participate in the study.Number of children whose parents consent for them to participate and number of children who did not have consent to participate.Number of participating children who leave the ELC setting after the study has begun.Attendance records of participating children will be collected throughout the study timeline to determine retention rates.

**RQ2** addresses whether matching on propensity score is feasible to detect changes in outcomes between exposure and comparison groups. This will be measured by:Number of children assigned a propensity score.Number of successful matches using propensity score.

A powered effectiveness evaluation can only be successful if its study design is able to detect differences in children’s health and wellbeing outcomes as a result of being exposed to outdoor nature-based play and learning. 

Addressing **RQ3** will identify which outcomes and measurement tools should be taken forward to the next stage of evaluation. This will be measured by:The completeness of the measurement assessments from baseline to follow-up.Which measurement tools demonstrate a positive, negative, or null effect between exposure and comparison groups from baseline to follow-up.The acceptability of the measurement tools within the study population.

The outcomes and their measurement tools can be found in Table 1. 

By examining the monitoring and evaluation (M&E) tools that are currently in place across ELC settings, we can determine whether similar outcomes are recorded among all participating ELC settings (**RQ4**); if so, it might be possible to develop a standardised method of analysing changes in outcomes. This approach could then be used in a powered effectiveness evaluation. **RQ4** will be measured by collecting a sample of M&E tools per recruited sample (*n* = 5), recording the outcomes that are monitored, and identifying whether analysis can be standardised.

**RQ 5 and 6** will be assessed through a **process evaluation** using qualitative interviews. Acceptability of the programme and study design methods will be measured based on the number of major barriers discussed during semi-structured interviews with ELC headteachers and practitioners. This will be conducted using the four components of the Normalisation Process Theory (NPT) [45]. See Appendix A for the interview guide and NPT components.

NPT identifies factors that support and impede the normalisation of complex interventions into routine practice [46,47]. The theory centralises on the work that individuals and groups do to allow an intervention or programme to become normalised. NPT has four primary components: *coherence* (sense making, such as how easy is it to understand the purpose of outdoor nature-based play and learning?); *cognitive participation* (or engagement, such as are practitioners committed to providing outdoor nature-based play and learning, are they supportive of the study recruitment methods?); *collective action* (are practitioners sufficiently trained to provide outdoor nature-based play and learning, are they committed to ensuring children remain in their study groups?); and *reflexive monitoring* (formal and informal appraisal of the programme and evaluation design). By using NPT, we can optimise the study design methods (recruitment, outcome measures) by determining whether the pilot study design was acceptable for practitioners and headteachers/managers. NPT will also help us understand to what extent outdoor nature-based play and learning is considered a part of everyday practice at participating ELC settings.

The progression criteria for RQs are discussed in the next section.

#### 2.8.1. Progression Criteria 

The CONSORT 2010 extension to randomised pilot and feasibility trial guidelines recommend setting out progression criteria when reporting feasibility and pilot studies [48]. In line with recommendations, our progression criteria will be assessed using a traffic light system with varying levels of acceptability, rather than strict thresholds [49,50,51]. For example, GREEN, strong indication that study design and programme is feasible and can be taken to the next stage of evaluation; AMBER, study design and programme could be feasible with some modifications; and RED, study design and programme should not progress forward without serious consideration and modification. The progression criteria for each RQ can be found in Table 3.

As demonstrated in Table 3, the progression criteria for **RQ1** have been informed by previous feasibility studies in this setting, where researchers have demonstrated a recruitment rate of 32%, 37%, and 10% of eligible ELC settings, respectively [31,32,33]. Our recruitment rate of at least 30% of contacted eligible ELC settings will demonstrate that our recruitment methods for ELC settings are feasible for a larger effectiveness evaluation. Moreover, to determine the feasibility of our participant recruitment methods, we aim to have at least 50% of eligible children at fully outdoor settings return a signed consent form and 25% of eligible children at all other settings return a signed consent. These estimates are different because we believe buy-in from parents at fully outdoor ELC settings will be greater than some of the traditional and satellite settings given the nature of the research project (exploring the impact of children playing outside). Additionally, parents choose to enroll their children at fully outdoor ELCs, whereas places at council-organised settings are assigned. Finally, if 80% or more participating children are retained at the study follow-up time period, the participant recruitment methods will be considered feasible to progress to an effectiveness evaluation. If less than 50%, the pilot study will be halted and will return to the design stage. If retention rates are between 50% and 79%, then the retention methods will be reviewed to determine whether they can improve before progressing to a powered effectiveness evaluation. 

The progression criteria for **RQ2** are also conditional upon which traffic light criteria are achieved regarding retention rates within **RQ1**. The number of retained children will undergo matching based on their propensity score. 

The traffic light criteria for **RQ3** are based on what we determine to be sufficiently acceptable to carry out analysis of the outcome data to detect an effect if one does exist. Outcome measures that can detect a signal in effect will be considered for progression to the next stage of evaluation subject to meeting the other progression criteria. These will also be considered alongside the number of barriers mentioned related to the measures in the interviews and feedback from parents/carers. The outcomes and their measurement tools are outlined in Table 4.

The traffic light criteria for **RQ4** are based on the extent to which analysis of M&E tools can be standardised across ELC settings. It is important for researchers to maximise the use of M&E tools that are already in place to reduce the burden on practitioners, increasing the likelihood of optimal participation and supporting evaluation capacity.

Finally, the progression criteria for **RQs 5 and 6** are based on the qualitative findings informed by NPT. If participants feel they have agency and resources to support outdoor play and learning and there are no major barriers associated with the study design, then progression to a powered effective evaluation will be possible after consultation with the research steering group.

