Children	Three years old at the time of recruitment or turning three during the study period (May to August 2022). Must spend at least three sessions per week (morning or afternoon sessions or all day) at the ELC setting included in the study. Children who have consent from their parents to participate. Specific to satellite settings: children who have attended their satellite outdoor space 3 times or less.	Not three years old at the time of recruitment or will not be three before the end of the study period (August 2022). Spend less than 3 sessions per week at the ELC under study. Have a serious injury or disability (e.g., wheelchair bound, broken leg, restricted arm movement) that would significantly limit their ability to engage in the study measurement methods. Children whose parent/carer does not provide informed consent to take part. Specific to satellite settings: children who have attended their satellite outdoor space more than 3 times.
ELC educators	Practitioners who supervise the children and support their play while outdoors. Managers/headteachers of participating ELC settings.	Practitioners who do not spend their working hours outside with the children when the children are outside (e.g., administrative staff).

**Table 3 ijerph-19-07461-t003:** Study criteria for progression to a powered effectiveness evaluation.

Feasibility and Pilot Study Criteria for Progression to a Powered Effectiveness Evaluation				
Research Question	Traffic light progression criteria	Recommendation if Green, Amber, or Red	Method of assessment	Rationale

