1. To what extent are the intended participants ***recruited*** to the study and are they ***retained***?	Recruitment: *ELC Settings* GREEN: at least 30% of contacted ELC settings express a willingness to participate. AMBER: 10 to 29%. RED: less than 10% of contacted ELC settings respond. *Participants* GREEN: fully outdoor ELC settings, at least 50% of eligible children return a signed consent form. At satellite and traditional ELC settings, at least 25% of eligible children return a signed consent form. AMBER: at least 50% of fully outdoor ELC settings achieve their 50% recruitment target. At least 50% of satellite and traditional ELC settings achieve their 25% recruitment target RED: Amber target is not achieved	GREEN: Strong indication to use the same recruitment process in full effectiveness evaluation. AMBER: Indication that recruitment process might work, but should be discussed with research steering group. RED: Indication that recruitment process needs serious revision before full effectiveness evaluation.	Data collected on eligible ELC settings and participants, response rates, and non-response rates.	Based on recruitment and retention rates of past feasibility studies in UK early years settings (Barber et al., 2019; Kipping et al., 2019; Malden et al., 2019).
	Retention GREEN: 80% or more participant retention rate. AMBER: 50–79% participant retention rate. RED: less than 50% participant retention rate.	GREEN: Strong indication to use the same recruitment process in full effectiveness evaluation. AMBER: Indication that recruitment process might work, but should be discussed with research steering group. RED: Indication that recruitment process needs revision before full effectiveness evaluation.		

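### Table 3's AMBER rule for child recruitment counts satellite and traditional settings together, so recruitment to the satellite exposure group can miss its target at both settings without turning the light RED

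*Protocol article*

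**What the plan says.** Section 2.2 (Study Design) describes three groups. Children at traditional settings are the controls, and they are matched with children from "two treatment groups: (1) 2 fully outdoors ELC settings and (2) 2 satellite ELC settings". Section 2.6 (Sample Size) gives the numbers: "We aim to recruit 2 fully outdoor ELC settings, 2 satellite ELC settings, and 2 traditional ELC settings".

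Section 2.8.1 (Progression Criteria) gives fully outdoor settings their own consent target of 50%. Every other setting shares one: "25% of eligible children at all other settings return a signed consent". The reason given is that parents at fully outdoor settings are expected to be keener on the study and have chosen their setting, whereas council places are allocated.

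Table 3, research question 1 (RQ1), turns this into a traffic light:
- GREEN needs at least 50% consent at fully outdoor settings. For the others: "At satellite and traditional ELC settings, at least 25% of eligible children return a signed consent form".
- AMBER needs at least half of the fully outdoor settings to reach their 50% target. For the others: "At least 50% of satellite and traditional ELC settings achieve their 25% recruitment target".
- RED applies only when AMBER is missed.

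For AMBER, Table 3 recommends taking the recruitment process to the research steering group.

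**The concern.** The joint count treats an exposure group and the control group as one unit. A shortfall in one can therefore be offset by success in the other, although the two are not interchangeable in the comparison. If satellite recruitment fails, the satellite contrast cannot be tried, and neither can propensity score matching with more than one treatment group, which is what research question 2 (RQ2) is about. A recruitment criterion should grade that outcome as a failure. As written, the middle grade can stand.

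**Working it through.** **Inputs**
- Settings per model: 2 fully outdoor, 2 satellite, 2 traditional (section 2.6). Check: 2 + 2 + 2 = 6, which agrees with the six settings in the Abstract.
- AMBER, fully outdoor part: at least 50% of 2 settings, so at least 1 (Table 3).
- AMBER, remaining part: at least 50% of 2 + 2 = 4 settings, so at least 2 (Table 3).
- RED: only if AMBER fails (Table 3).

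**The direct case.** Let both traditional settings reach 25% and neither satellite setting do so. The remaining part is (0 + 2)/4 = 50%, which meets the rule. With at least 1 of 2 fully outdoor settings on target, AMBER is reached and RED is excluded. The satellite consent rate does not enter beyond being below 25%; it may be 0%.

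**All patterns.** Mark each of the six settings as on or off its target: 2^6 = 64 patterns.
- Fully outdoor part met: 3 of 4 patterns (all except both off target).
- Remaining part met: C(4,2) + C(4,3) + C(4,4) = 6 + 4 + 1 = 11 of 16 patterns.
- AMBER threshold met: 3 × 11 = 33 of 64.
- Of these, no satellite setting on target: both traditional settings must be on, which is 1 pattern, times 3 = 3.
- Of these, no traditional setting on target: likewise 3.

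**With the rule applied to each model.** At least 1 of 2 settings is needed in each of the three models: 3 × 3 × 3 = 27 patterns. The 33 − 27 = 6 patterns that drop out are exactly the 3 + 3 above, and they become RED. No pattern moves to a better grade.

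**Would another criterion in Table 3 catch an empty satellite group?**
- Setting recruitment is a share of contacted settings and is not split by model.
- Retention is a share of participating children, so children never recruited do not lower it.
- RQ2 is a share of enrolled children who are matched. Fully outdoor and traditional children could be matched at 80% or more with no satellite child present.
- The minimum of 10 children per setting is an aim in section 2.6 and does not appear in Table 3.

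The reverse case differs on one point. With no traditional child at all there would be no one to match to, so RQ2 would itself fail. Traditional consent that is merely below 25% would not guarantee that.

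**The case against.** The strongest reply is that RQ1 tests a recruitment process, and that grouping settings by expected consent suits a consent-rate criterion. Section 2.8.1 does give a reason for the two rates. That supports using 25% for both satellite and traditional settings. It does not support letting one model's settings stand in for the other's.

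Three further points limit the concern, and they stand:
- AMBER is not a clear go. Section 2.8.1 describes it as feasible subject to modification, and Table 3 sends it to the steering group. Section 2.8 records approached and consenting children across all participating settings, so the group would see an empty satellite arm.
- Missing the target is not the same as recruiting no one. A satellite setting at 20% consent is off target but still supplies children.
- The AMBER result also depends on at least one fully outdoor setting reaching 50%.

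A reader might go further and infer that the light could be GREEN with no satellite child, by taking the 25% in "At satellite and traditional ELC settings, at least 25% of eligible children return a signed consent form" over all satellite and traditional children together. The wording allows that reading, but the documents do not establish it. The AMBER rule speaks of settings reaching their own target, which points to 25% per setting, and then 0% at a satellite setting cannot be GREEN. Nor can one say that traditional children would dominate a pooled rate. Section 2.4 gives enrolment by sector, not by model. The satellite-only eligibility limit, "Specific to satellite settings: children who have attended their satellite outdoor space 3 times or less", reduces the eligible number only relative to that setting's own roll. The GREEN wording is an ambiguity, not a shown error.

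**Conclusion.** The point holds for AMBER on the plain wording of Table 3 and the planned two settings per model. It would fall only if the rule were meant as half of each model, which the text does not say. The size is 3 of 33 qualifying patterns in each direction. How likely these are cannot be derived, because the documents give neither eligible numbers nor expected consent by model. The consequence is a decision rule that leaves failed satellite recruitment to the steering group's judgement when the criteria are meant to make that decision explicit. It is not evidence that satellite recruitment will fail, nor that such a failure would go unseen.

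**What to change.** In section 2.8.1 and in Table 3 (RQ1, participants), keep the targets at 50% for fully outdoor, 25% for satellite and 25% for traditional settings, and change how they are combined:
- Apply the 25% target, and the AMBER rule that at least half of the settings reach it, to satellite settings and to traditional settings separately.
- Report the child-recruitment light as the worst of the three models.
- Say in the GREEN rule whether the target applies to each setting or to all eligible children within a model. Either version excludes GREEN with no satellite consents, because 0% is below 25%.

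The cost is about one sentence in each place and no new data. There are two downsides. The light can be less favourable than under the joint rule. And with two settings per model each AMBER decision rests on 1 of 2 settings, so the consent count and denominator for each setting should be reported beside the light.
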